**Design and methods:**

This is a randomized controlled trial. Seventy-two PSUI patients between 42 days and 1 year postpartum will be randomly assigned in a 1:1 ratio to either the acupuncture group (n = 36) or the sham acupuncture group (n = 36). Both groups will receive acupuncture treatments three times per week for two weeks. Both groups will receive identical education regarding pelvic floor muscle training. The primary outcomes are changes in urine leakage volume measured by 1-hour pad test at week 2 of treatment and week 6 of follow-up compared to baseline (week -1), and the proportion of patients achieving at least 50% reduction in urine leakage volume at week 2 compared to baseline. Secondary outcomes include 72-hour bladder diary, The International Consultation on Incontinence Questionnaire-Short Form (ICIQ-SF), Incontinence Quality of Life questionnaire (I-QOL), and pelvic floor muscle strength assessment.

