Traditional Chinese medicine offers various SUI treatments, with acupuncture showing the most promising results. A 504-patient RCT found electroacupuncture significantly reduced urine leakage and improved quality of life in middle-aged/elderly women, with clear clinical efficacy and safety [9]. PSUI differs from general SUI, as PSUI is caused by pelvic floor and supporting structure damage from pregnancy/childbirth, while SUI often results from pelvic organ prolapse or muscle weakness. Therefore, the symptoms and treatments for PSUI and SUI are not entirely identical. Previous research has explored acupuncture for PSUI, but evidence on its efficacy is limited [10–12]. High-quality randomized controlled trials are needed to thoroughly evaluate the effectiveness and safety of acupuncture for PSUI treatment. Positive findings could provide a new clinical approach for PSUI while bolstering Traditional Chinese Medicine’s application in modern medicine.

This pilot trial aims to provide evidence that acupuncture has therapeutic effects on PSUI beyond placebo. Prior studies lack sham-controlled acupuncture as a comparator for PSUI [10–12]. To our knowledge, this will be the first acupuncture trial using non-acupoint, shallow, and non-deqi needling as a sham control to rigorously evaluate acupuncture’s efficacy for PSUI. If the true acupuncture group shows superior results, it would preliminarily confirm acupuncture’s therapeutic benefits and inform future formal trials.

The primary objective of this trial is to verify the feasibility of the protocol, defined as meeting the following criteria: (1) dropout rate ≤20%; (2) compliance rate ≥80%; (3) data completeness ≥90%; (4) adverse event rate <5%, with no intervention-related serious adverse events. The secondary objective is to collect preliminary parameters for sample size calculation, including: (1) mean between-group difference in the 1-hour pad test; (2) standard deviation of outcome measurements; (3) estimated effect size (Cohen’s d).

Two hypotheses are proposed: (1) Acupuncture can reduce urine leakage volume in patients with PSUI; (2) Acupuncture is a safe intervention for treating PSUI.

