## Methods

### Study design

This is a pragmatic, single-center, two-arm, randomized controlled trial conducted in China. A total of 72 postpartum women with stress urinary incontinence will be randomly allocated in a 1:1 ratio to an acupuncture group and a sham acupuncture group. The trial duration is six weeks, including a two-week treatment period and a four-week follow-up. The study protocol has been approved by the Ethics Committee of Beijing University of Chinese Medicine Third Affiliated Hospital (Approval No. BZYSY-2024KYKTPJ-23) and registered on the International Traditional Medicine Clinical Trial Registry platform (ITMCTR, [http://itmctr.ccebtcm.org.cn/]) with registration number ITMCTR2024000290 (Date: August 24, 2024, version 4.0). The trial design adheres to the Standards for Reporting Interventions in Clinical Trials of Acupuncture (STRICTA) [13] and the Standard Protocol Items: Recommendations for Interventional Trials (SPIRIT) guidelines [14]. Fig 1 illustrates the SPIRIT schedule, and S1 File shows the SPIRIT checklist. Fig 2 illustrates the flow chart of this trial.

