### Sample size

This study is a pilot trial, and for acupuncture clinical research, a sample size of 30 cases per group in pilot trials is suitable for parameter estimation [17], with a 20% dropout rate taken into consideration. Therefore, this study will enroll 36 subjects per group, for a total of 72 subjects.

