### Statistical analysis

Statistical analysis will be performed using SPSS software version 26.0. Measurement data will be presented as means and standard deviations (SD) or medians and interquartile ranges (IQR), as appropriate. Counting data will be expressed as percentages.

Efficacy evaluation will adhere to the intention-to-treat (ITT) principle, including all patients who have received at least one treatment. For the primary outcome (1-hour pad test) and secondary outcomes (72-hour bladder diary, ICIQ-SF scores, I-QOL scores, pelvic floor muscle strength test results, and patient self-evaluation of efficacy), a mixed-effects model will be employed to account for the characteristics of repeated measures data. The model will include group, time points, and their interaction as fixed effects, with participants treated as random effects. Baseline values will be incorporated as covariates.

Missing data will be handled using multiple imputation. Five datasets will be generated based on age, sex, body mass index (BMI), baseline characteristics, and outcome values at other time points for analysis. Two sensitivity analyses will be performed for the primary outcome (1-hour pad test): (1) an analysis of the dataset without imputation to assess potential bias introduced by imputation and (2) an analysis of the per-protocol (PP) set to evaluate the impact of adherence. The PP set is defined as participants who completed at least 80% of the planned treatments without significant protocol violations (i.e., at least five treatments in both the acupuncture and sham acupuncture groups).

Safety analysis will include all participants who received at least one treatment. AE rates will be described using counts and percentages. Between-group comparisons will be conducted using the chi-square test when the expected frequency requirements are met; otherwise, Fisher’s exact test will be used. All statistical analyses will be two-tailed, with a significance level of *P *< 0.05 considered statistically significant.

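### Randomised group is missing from the stated multiple-imputation predictors, so the between-group difference is pulled toward zero, by an amount that depends on how much is missing and when

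*Protocol article*

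**What the plan says.** The Statistical analysis section states: "Missing data will be handled using multiple imputation". It then names the number of imputations and the predictors: "Five datasets will be generated based on age, sex, body mass index (BMI), baseline characteristics, and outcome values at other time points for analysis". Treatment group is not on the list, and imputation within arm is not mentioned.

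The same section describes the analysis model: "The model will include group, time points, and their interaction as fixed effects, with participants treated as random effects". Baseline values are added as covariates. The model serves the 1-hour pad test and all listed secondary outcomes, in women who had at least one treatment.

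The abstract gives the primary pad-test outcome as "changes in urine leakage volume measured by 1-hour pad test at week 2 of treatment and week 6 of follow-up compared to baseline (week -1"). The only check on the imputation is a sensitivity analysis confined to the pad test: "an analysis of the dataset without imputation to assess potential bias introduced by imputation".

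Two other statements set the scale. The Sample size section works "with a 20% dropout rate taken into consideration", and the feasibility criteria in the Introduction accept dropout up to 20% and ask for data completeness of at least 90%. The Introduction also names the between-group pad-test difference, the SD and Cohen's d as the parameters to be collected for sizing the formal trial.

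**The concern.** An imputation model should contain at least the terms that the analysis model estimates. Here it lacks the one term of interest. A missing outcome is predicted from a regression fitted to both arms together, so part or all of the arm difference is lost in the filled-in values, and the completed data set then understates the difference.

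The phrase about baseline characteristics cannot reasonably be read as covering the assigned arm. The Exploratory analysis section uses the same term for age, BMI and pelvic floor muscle strength.

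This pilot exists partly to supply an effect size. The required sample size varies as 1/d², so a systematic understatement of d enlarges the next trial or makes it look less worthwhile than it is. The responder outcome at week 2 would be pulled the same way if it is derived from imputed leakage.

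**Working it through.** The plan gives no figure for imputation bias to reproduce. The one related figure does reproduce: 30 × 1.20 = 36 per arm, which is where the 20% allowance enters. At 20% missing, about 36 × 0.20 = 7 women per arm would be imputed.

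**Inputs from the article:** 36 per arm, 1:1; pad test at baseline, week 2 and week 6; 5 imputations; missing share *m* = 20% (dropout allowance) or 10% (the complement of the 90% completeness target).

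**Assumptions not in the article:** normal outcomes with SD 1, the same true difference *d* = 0.5 SD at both visits, a common correlation ρ of 0.3, 0.5 or 0.7 between visits, and data missing completely at random.

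**Step 1. No post-baseline value.** The prediction uses baseline variables only, and these are balanced by randomisation. The expected arm difference among imputed values is 0, so the overall difference is about (1 − m)·d. Shrinkage ≈ m: 10% or 20%.

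**Step 2. Week 2 observed, week 6 missing.** The observed week-2 value carries part of the arm effect. With group omitted, the coefficient of week 2 given baseline is

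β = (ρ − ρ² + d²/4) / (1 − ρ² + d²/4),

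and the imputed arm difference is β·d. Shrinkage = m(1 − β), with 1 − β = (1 − ρ)/(1 − ρ² + d²/4). Here d²/4 = 0.0625.

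- ρ = 0.3: 0.7/0.9725 = 0.720, giving 7.2% at m = 10% and 14.4% at m = 20%.
- ρ = 0.5: 0.5/0.8125 = 0.615, giving 6.2% and 12.3%.
- ρ = 0.7: 0.3/0.5725 = 0.524, giving 5.2% and 10.5%.

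The assumed *d* matters little. As d approaches 0, 1 − β tends to 1/(1 + ρ), which for ρ = 0.5 and m = 20% gives 13.3% in place of 12.3%.

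**Step 3. Simulation.** 1,500 replicates per scenario, Bayesian regression imputation with 5 data sets, then regression on group and baseline. Each row shows estimates for ρ = 0.3 / 0.5 / 0.7; the truth is 0.50.

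| Missing pattern (estimate) | m | Group omitted | Group included | Shrinkage, omitted against included |
|---|---|---|---|---|
| All post-baseline (week 2) | 10% | 0.450 / 0.445 / 0.451 | 0.502 / 0.496 / 0.503 | 10.4 / 10.3 / 10.3% |
| All post-baseline (week 2) | 20% | 0.389 / 0.397 / 0.398 | 0.492 / 0.502 / 0.503 | 20.9 / 20.9 / 20.9% |
| Week 6 only (week 6) | 10% | 0.461 / 0.474 / 0.478 | 0.501 / 0.508 / 0.504 | 8.0 / 6.7 / 5.2% |
| Week 6 only (week 6) | 20% | 0.426 / 0.445 / 0.440 | 0.501 / 0.510 / 0.494 | 15.0 / 12.7 / 10.9% |

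These agree with steps 1 and 2. Complete-case estimates were also 0.49–0.51 throughout.

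The simulation analyses each visit separately instead of fitting the planned mixed model. Once imputed, the data are complete at every visit, and the group contrast at a visit is again a baseline-adjusted difference in means, so the attenuation carries over.

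**Step 4. Consequence for the formal trial.** With the SD unchanged, required N is multiplied by 1/(1 − shrinkage)²: 1/0.95² = 1.11, 1/0.90² = 1.23, 1/0.89² = 1.26 and 1/0.79² = 1.60.

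**The case against.** The strongest reply has five parts.

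- **Later values help.** A reader might infer that every imputed outcome is drawn as if treatment had no effect. The list does not support that, because it includes outcomes at other time points. The inference is exact only for women with no post-baseline value. This stands, and it is why the size is a range.
- **20% is the upper end.** It requires the full dropout allowance and every loss before week 2. The article gives no split of dropout timing, four of the six weeks are follow-up, and women never treated are outside the analysis set. If the 90% completeness target is met, the bias on a 0.5 SD effect is about 0.02–0.06 SD, against a standard error near √(2/36 × 0.75) = 0.20 SD at ρ = 0.5. This also stands, but the bias is systematic and avoidable, and the plan should hold at the dropout it accepts.
- **A check is planned.** The analysis without imputation could reveal the discrepancy, and under data missing completely at random it would be about right. The Introduction does not say that the planning parameters must come from imputed data. But the check covers the pad test only and leaves the main estimate as it is.
- **Power.** A reader might infer a serious loss of power. The article sets no power target: it is sized for parameter estimation, has feasibility as its primary objective, and concedes that the sample may be too small for definitive conclusions. Any power figure would rest on an assumed effect.
- **The full analysis plan is not shown.** It may add group. That would not make the published list right as it reads.

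A reader might also fault two further items on the list. Sex is constant here ("A total of 72 postpartum women with stress urinary incontinence will be randomly allocated in a 1:1 ratio"), so it adds nothing and harms nothing. Five imputations cost little: in a simulation at 20% missing, the mean confidence-interval width was 0.966 with 5 and 0.938 with 20, about 3% apart. Neither is a defect of substance.

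**Conclusion.** The point holds in this limited form. The stated imputation model leaves out randomised group while the analysis model estimates it, so the rule as written is wrong and is not merely short of detail. The effect is attenuation of the between-group difference: about 5–10% at 10% missing and 11–21% at 20% missing. The lower ends apply when only week 6 is missing and the upper ends when all post-baseline values are missing. With group included, the estimate was 0.49–0.51 SD against a truth of 0.50.

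The range rests on normal outcomes, data missing completely at random, a 0.5 SD effect equal at both visits and correlations of 0.3–0.7. Other missingness mechanisms could add bias of their own. The documents do not support saying that the effect is erased, that the 20% figure is the expected loss, or that the trial's conclusions fail on power.

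**What to change.** In the Statistical analysis section, add treatment group to the imputation predictors for every outcome and visit, or state that imputation is done separately by arm. Entering group as a predictor in the equation for each visit lets its effect differ by visit, which matches the group by time term. With 36 women per arm, it also asks less of the data than separate models by arm.

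The cost is one sentence and no extra data. Analysts stay blinded, because the Blinding section already gives them A/B codes and the analysis model needs those codes anyway.

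Deleting sex is only tidying. Raising the number of imputations is optional and of minor effect.

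### Five imputed datasets leave avoidable seed-to-seed noise in the main efficacy analysis; it matters only near the 0.05 threshold, and at least 50 would remove most of it

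*Protocol article*

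**What the plan says.** Under Statistical analysis, the protocol article states "Missing data will be handled using multiple imputation" and then "Five datasets will be generated", drawing on demographic and baseline variables and on the outcome at other visits. The same section says "All statistical analyses will be two-tailed", with the threshold at 0.05. An analysis of the pad test without imputation is planned, but only as a sensitivity analysis.

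Under Sample size, the target of 30 per group is raised "with a 20% dropout rate taken into consideration", so that "this study will enroll 36 subjects per group, for a total of 72 subjects". The feasibility criteria in the Introduction accept dropout of up to 20% and ask for at least 90% data completeness. The protocol itself therefore contemplates roughly 10 to 20% missing data. The article gives no reason for choosing five.

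**The concern.** A multiply imputed result depends on random draws. With few imputations, the pooled estimate moves when the imputation is run again on the same data with another seed. The usual defence of five is that it costs little average precision. That is true, but it does not say how far one trial's reported estimate and p-value would shift on a re-run.

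The imputed analysis is the main efficacy analysis and is read against 0.05. The Introduction says that superior results would preliminarily confirm a benefit, and it lists the mean difference and Cohen's d as inputs to the formal trial. If the pad-test result lands near the threshold, part of what is reported would be noise from the imputation that could have been avoided.

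**Working it through.** **Inputs from the protocol article.** Number of imputations m = 5; two-sided 0.05 (Statistical analysis). 36 per group, 72 in total; 20% dropout (Sample size). Dropout up to 20% and completeness of at least 90% (Introduction).

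**Assumed.** The FMI is not given. It is taken as roughly the missing fraction, 0.10 to 0.20. The test statistic is treated as normal.

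**The plan's own figure.** 30 × 1.2 = 36 per group, as stated. Twenty per cent of 72 is about 14 participants. The article gives no Monte Carlo error to reproduce.

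**Step 1: seed-to-seed SD of the pooled estimate, in standard errors = √(FMI/m).**
- m = 5: √(0.10/5) = 0.141; √(0.20/5) = 0.200
- m = 50: √(0.10/50) = 0.045; √(0.20/50) = 0.063

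**Step 2: spread of p when the underlying p is 0.05.** The central 95% of seeds give z = 1.96 ± 1.96 × SD. For example, with FMI 0.20 and m = 5, z runs from 1.96 − 0.392 = 1.568 to 1.96 + 0.392 = 2.352, so p runs from 0.117 down to 0.019.

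| FMI | m = 5 | m = 50 |
|---|---|---|
| 0.10 | 0.025 to 0.092 | 0.041 to 0.061 |
| 0.20 | 0.019 to 0.117 | 0.037 to 0.066 |

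**Step 3: chance that one run gives the other verdict from a very large m.** For an underlying z this is Φ(−|z − 1.96|/SD). At p = 0.04, z = 2.054 and the distance to the threshold is 0.094. With m = 5 the chance is Φ(−0.094/0.141) = 25% (FMI 0.10) or Φ(−0.094/0.200) = 32% (FMI 0.20). With m = 50 it is 2% or 7%. Away from the threshold it fades: with FMI 0.20 and m = 5 it is 3% at p = 0.02, 6% at p = 0.10 and about 0.1% at p = 0.01.

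**Step 4: the same chance averaged over all results a trial might give** (range is FMI 0.10 to 0.20).

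| True situation | m = 5 | m = 50 |
|---|---|---|
| No effect | 1.3 to 1.9% | 0.4 to 0.6% |
| 50% power | 4.5 to 6.3% | 1.4 to 2.0% |
| 80% power | 3.2 to 4.5% | 1.0 to 1.4% |

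**Step 5: interval width at FMI 0.20, relative to very large m.** The standard error grows by √(1 + 0.20/5) = 1.020. Assuming 68 complete-data degrees of freedom, the observed-data value is (69/71) × 68 × 0.8 = 52.9. With m = 5 it combines with 4/0.20² = 100 to give 1/(1/100 + 1/52.9) = 34.6. The t multiplier rises from 2.006 to 2.031. The product is 1.020 × 2.031/2.006 = 1.033, about 3% wider. With m = 50 the excess is 0.3%.

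**Step 6: effect size.** With 36 per group the sampling SE of Cohen's d is about √(2/36) = 0.236. Seed noise at FMI 0.20 and m = 5 is 0.20 × 0.236 = 0.047. The total SD rises by the factor √(1 + 0.20²) = 1.020, or 2%.

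**Simulation check.** Trials of 72 were simulated with values missing completely at random, between-visit correlations of 0.5 to 0.6, and a baseline-adjusted contrast at the last visit standing in for the mixed model. Sixty borderline trials (large-m p between 0.04 and 0.06) were kept per scenario. The 95% range of p across seeds at m = 5 was 0.024 to 0.109 with 10% missing and 0.017 to 0.161 with 20% missing. At m = 50 it was 0.040 to 0.063 and 0.036 to 0.072. These are a little wider than the formula gives, and they lead to the same conclusion.

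**The case against.** The strongest case on the other side is that this hardly matters here, and much of that stands.

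- **The inference is valid.** Rubin's rules already add the between-imputation term divided by m to the variance. The 3% in width is the average price of the noise, and coverage is not at fault.
- **No decision rests on p < 0.05.** The success criteria in the Introduction are dropout, compliance, completeness and adverse events. The Discussion concedes that the sample may be too small for firm conclusions. The Abstract lists more than one primary pad-test result, so there is no single primary p-value.
- **Effect-size planning is barely touched.** Sampling error dwarfs the seed noise (Step 6).
- **An FMI of 0.20 is the upper end.** The 20% covers the whole six weeks, the completeness target is 90%, and imputation from other visits recovers some information.
- **The analysis without imputation has no seed** and could expose an unstable result.

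These points limit the consequence but do not remove the noise. The analysis without imputation is secondary, and comparing it with the imputed result is less clear when the imputed result itself moves by 0.14 to 0.20 standard errors between seeds.

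A reader might go further and infer that the trial's result would not be reproducible, or that the seed would usually decide significance. The documents do not support that. The verdict is unstable only if the result happens to fall near 0.05, and a recorded seed makes the run repeatable. Seed recording commonly sits in the analysis plan or program, neither of which is shown, so its absence from the article is no fault.

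**Conclusion.** The point holds as a minor, free improvement. It concerns a number that the article states, not a detail left to another document. At the missingness the protocol allows, five imputations carry about three times the seed noise of 50, since √(50/5) = 3.2. The practical effect is a different verdict from a very large m in about 1 to 6% of trials, reduced to 0.4 to 2% with 50, and a materially unstable p-value only close to the threshold.

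This rests on an FMI of 0.10 to 0.20 and a normal approximation. If little is missing, or the result is far from 0.05, five does no harm. If p is almost exactly 0.05, no finite number of imputations settles the verdict; a larger number only narrows the zone. The planned intervals are not invalid, and the feasibility objective is unaffected.

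**What to change.** In the Statistical analysis section, replace five with at least 50 imputed datasets. Nothing changes for participants, visits, outcomes or sample size. The cost is one number in the plan and a few minutes of computing.

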### Exploratory analysis

Exploratory analysis will be conducted to explore potential correlations between treatment outcomes and baseline characteristics. Multiple linear regression models will be used, with key outcomes (e.g., change in 1-hour pad test results, ICIQ-SF scores, and I-QOL scores) as dependent variables. Independent variables will include baseline characteristics such as age, BMI, pelvic floor muscle strength, and other relevant factors. Results will be presented as regression coefficients with 95% confidence intervals. This analysis aims to identify predictors of treatment response and potential moderating factors.

